### Randomization and concealment of allocation

Patients who consent to participate will be randomized (1:1 allocation ratio) between the intervention and usual care using a stratified permuted block randomization method using block sizes of 4,6 and 8. Stratification is based on gender to ensure equal distribution in both groups. The allocation sequence is generated by an independent statistician a priori and will be kept concealed from the study team. Randomization will be done using the REDCap randomization module based on the allocation sequence and allocation will be locked once assigned. Randomization and intervention allocation will only be performed by the study team after the patient is counselled fully about the study and provides informed consent.

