### Sample size calculation

The sample size needed to detect a 10-point difference between the intervention arm and usual care arm in KOOS_4_ was 41 patients in each arm based on a power of 90%, *p*-value of 0.05 (two-sided) and a standard deviation of 14. The anticipated population KOOS_4_ and standard deviations were based on the initial pilot study [25] done and the minimally clinically important difference on 10-points (MCID) for KOOS [24]. In order to account for a missing data rate of 20%, 100 patients will be recruited for the study.

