### Analysis plan

The primary endpoint in this study is KOOS_4_ at 12-month follow-up. Results will be analysed by intention-to-treat (ITT) principle. However, data will also be analysed by per-protocol (PP) approach to account for protocol violations such as patients who were deemed not compliant to treatment or patients who underwent a surgical procedure of the knee due to treatment failure during the course of the study.

Descriptive frequency analysis will be used for baseline characteristics. For continuous variables, the mean and standard deviation will be reported and for categorical variables, the frequencies and percentages will be reported. Between-group comparisons of change from baseline to 1-year follow-up in the primary and secondary continuous outcomes will be analysed using a generalized linear mixed model (GLMM). Testing for normality of distributions of outcomes will be based both on the Shapiro-Wilks test and a visual analysis of the histogram plot. Categorical secondary outcomes will be analysed using the ordinal logistic regression function under GLMM. A two-sided *p*-value less than 0.05 will be considered as statistical significance. An analysis will be done on the nature of the missing data to determine if the data was missing at random or a systemic bias was present resulting the missing data.

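### The planned missing-data check cannot separate missing at random from missing not at random, so it cannot validate the assumption behind the primary mixed model

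*Protocol article*

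**What the plan says.** Under Analysis plan, the article sets the endpoint: "The primary endpoint in this study is KOOS_4_ at 12-month follow-up". Analysis is by intention to treat, with a per-protocol analysis alongside. Continuous outcomes, the primary one included, are compared between arms with a generalized linear mixed model (GLMM). The section ends with its only statement on missing data, an analysis of their nature "to determine if the data was missing at random or a systemic bias was present". It names no method for this and no action that follows from the answer.

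Under Sample size calculation, missing data appear as a recruitment margin: "In order to account for a missing data rate of 20%, 100 patients will be recruited for the study". Under Outcomes, measurements are scheduled at baseline and at 3, 6 and 12 months. Table 4 (RE-AIM framework) lists reasons for withdrawal among the data to be collected.

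**The concern.** The sentence promises a finding that the data cannot deliver. Whether scores are missing at random, given what was observed, depends on the missing scores themselves. A mixed model fitted by likelihood is valid if that assumption holds and the model uses the relevant observed data. It does not need the assumption to be proven, and this check cannot prove it.

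The two alternatives offered are also not opposites. Missingness that differs systematically by arm or by 3-month score can be missing at random given those variables. Missingness that shows no pattern in the observed data can still depend on the unseen score.

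The point has some weight in this trial. Patients know their arm, since only the outcome assessors are described as blinded. KOOS4 reflects patients' own reports. The arms ask different things of patients: scheduled group sessions in one, physiotherapy at the discretion of patient and physiotherapist in the other. Under General outcomes, trial participation ends after a serious adverse event. Read literally, that could link missing scores to health. None of this shows that dropout will be informative, but it makes the question worth handling correctly.

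**Working it through.** **Inputs.** Sample size calculation gives a 10-point target ("detect a 10-point difference between the intervention arm and usual care arm"), 41 per arm, 90% power, and a significance level "of 0.05 (two-sided) and a standard deviation of 14". Randomization and concealment of allocation gives equal allocation ("randomized (1:1 allocation ratio"). The missing-data allowance is 20% and the total is 100.

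**1. Reproduce the plan's figures.**
- n per arm = 2 × [14 × (1.960 + 1.282) / 10]² = 41.19, which rounds up to 42. The stated 41 gives 89.9% power, so it reproduces within rounding.
- Total with allowance: 82 / 0.80 = 102.5, so 103; or 82 × 1.20 = 98.4, so 99. The stated 100 lies between them.
- If 20% of 100 are missing, 80 remain, or 40 per arm, with 89.1% power (normal approximation).

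The allowance therefore covers the loss of precision. It does not address bias.

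**2. What the check can show.** Missing at random means that, given arm, baseline and earlier scores, the chance of a missing 12-month score does not depend on that score. Testing this needs the 12-month scores of patients who have none.

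| Result of the check | Conclusion the sentence invites | What is actually known |
|---|---|---|
| Missingness unrelated to arm, baseline or earlier KOOS4 | Missing at random | No evidence against missing completely at random; dependence on the unseen score remains possible |
| Missingness related to arm, baseline or earlier KOOS4 | Systematic bias | Not missing completely at random; may still be missing at random given those variables |

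Neither row supports the conclusion the sentence invites.

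**3. Size of a departure (illustrative).** Let f be the missing fraction in an arm, and δ the amount by which its unseen scores are worse than the model predicts. The shift in the treatment difference is f × δ. The values of δ are assumptions; the documents give none.
- Intervention arm only, f = 0.20: 0.20 × 5 = 1, 0.20 × 10 = 2, 0.20 × 15 = 3 points, which is 10% to 30% of the 10-point target.
- Opposite departures in the two arms: 0.40 × 5 = 2, 0.40 × 10 = 4 points.
- Equal departures in the same direction with equal missing fractions: the shifts cancel.

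**4. Where the conclusion would change.** With 40 observed per arm and SD 14, SE = 14 × √(2/40) = 3.13, and the 95% half-width is 1.96 × 3.13 = 6.14. Holding the SE fixed, the one-arm tipping point is (observed difference − 6.14) / 0.20.
- Observed difference 10: 3.86 / 0.20 ≈ 19 points.
- Observed difference 8: 1.86 / 0.20 ≈ 9 points.

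A range of shifts ending at 15 would not reach the first of these, because 10 − 0.20 × 15 = 7, still above 6.14. These are rough values. They ignore covariate adjustment, the repeated measures and imputation variance.

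**The case against.** The best defence is that the sentence is loosely worded rather than wrong. In ordinary use it may mean comparing patients with and without data to see whether loss is haphazard or patterned. That comparison is feasible and useful, and the recorded reasons for withdrawal would help judge whether informative dropout is plausible. Nor does the sentence drive a decision: intention to treat and the GLMM are fixed whatever it finds. This stands as a limit on the weight of the point. It does not rescue the wording, because even the looser check cannot support either conclusion the sentence offers.

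A reader might go further and infer that the primary result has no valid check at all. The documents do not support that. A journal article commonly leaves sensitivity analyses to the statistical analysis plan or full protocol, and neither is shown. A reader might also take the 20% as a forecast that one patient in five will be lost; it is a recruitment margin.

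Two further objections hold in part. Missed sessions are non-compliance, not missing outcomes, so a link from attendance burden to missing 12-month scores is plausible but not shown. And an observed 10-point difference would withstand a one-arm shift larger than the planning SD of 14. A difference of 8 would not.

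**Conclusion.** The point holds as a fault in what the article states. The promised analysis cannot determine whether data are missing at random, so it cannot validate the assumption behind the primary model and may mislead in either direction. The primary GLMM itself is not at fault. If it is fitted by likelihood and includes the 3- and 6-month scores, it is valid under missing at random; the article does not state its visit structure.

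The size is conditional. A shift of 1 to 3 points rests on 20% missing and assumed departures of 5 to 15 points in one arm only. The tipping points of about 19 and 9 points rest on 40 observed per arm, SD 14 and a fixed SE. A large effect would be robust and a moderate one might not be; a tipping-point analysis would show which, and the stated check cannot. The correction is worth making, but the fault does not invalidate the trial.

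**What to change.** Replace the sentence with three statements.

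1. The primary model assumes that 12-month KOOS4 is missing at random given arm, baseline KOOS4 and earlier KOOS4 scores.
2. Missingness and reasons for withdrawal will be described by arm, baseline and earlier scores, with no claim to establish the mechanism.
3. A prespecified delta-adjusted tipping-point analysis of 12-month KOOS4 will shift the imputed scores, first in the intervention arm only and then in both arms. The range will be wide enough to reach the point where the conclusion changes. On the planning figures, that means going past about 19 points if the observed difference is 10, and past about 9 if it is 8.

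If the statistical analysis plan already contains such an analysis, a cross-reference replaces the third statement. No new data, patients or design changes are needed. The cost is a short rewrite and one extra analysis to run and report.

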### Data management

All data will be monitored by the PI or the study team, independent on the study sponsor. Data quality measures include queries to identify outliers and missing data. A unique identifier will be assigned to each subject after enrolment to ensure patient confidentiality. Data will be collected and stored on the Research Electronic Data Capture (REDCAP) system which is a widely used and secure web application for clinical data management in research. The REDCAP system is password protected and will only be accessible by the study team.

## COMPONENT 2: economic evaluation

### Aim and study design

The aim of the economic evaluation is to evaluate the cost-effectiveness of a personalized, community based 12-week multidisciplinary program for patients with knee OA. The Panel on Cost-Effectiveness in Health and Medicine recommends the use of a societal perspective to ensure that potentially important indirect costs such as productivity and caregiver cost would not be omitted [68]. The study will be conducted from a societal perspective to determine the cost-effectiveness of the intervention [68]. Results from the economic evaluation will be reported based on the Consolidated Health Economic Evaluation Reporting Standards (CHEERS) Statement [69].

### Cost estimation and outcome measurement

Cost data will be collected via hospital administrative databases and patient-reported questionnaires to estimate direct medical, direct non-medical and indirect costs. Indirect costs include health-related productivity loss due to knee OA [70] from absenteeism and presenteeism, measured with the Work Productivity and Activity Impairment Questionnaire (WPAI) [71]. The scope of the cost data collection was based on the validated OA Cost and Consequences Questionnaire (OCC-Q) [72] and adapted to the Singapore context to ensure that all relevant sources of cost were collected. The cost questionnaire used can be found in Additional file 3. Cost data will be collected at 3 monthly intervals till 1-year follow-up.

The primary measure of health benefit will be Quality of Life Years (QALYs) measured using the EQ-5D [51]. The incremental cost-effectiveness ratio (ICER) over the trial period of this multidisciplinary non-surgical community-based program for knee OA compared to usual care will be determined.

## COMPONENT 3: implementation and evaluation framework

### RE-AIM framework

The RE-AIM framework has been proposed as an appropriate model to strengthen the case for policy change and implementation for knee OA [11]. A recent study in Canada in 2018 used the RE-AIM model to evaluate the cross-cultural adaption and implementation of the GLA:D program [30] for hip and knee OA [73]. Table 4 outlines the definition and proposed data collection based on the RE-AIM criteria.

**Table 4 Tab4:** RE-AIM framework and Data Collection

Dimension	Definition	Data Collection
Reach	The absolute number, proportion, and representativeness of individuals who are willing to participate in a given initiative, intervention, or program.	CONSORT flow Eligibility Log and reasons for non-participation Reasons for withdrawals Qualitative methods
Effectiveness	The impact of an intervention on important outcomes, including potential negative effects, quality of life, and economic outcomes.	Primary and secondary outcomes Adverse outcomes Economic Evaluation
Adoption	The absolute number, proportion, and representativeness of settings and intervention agents (people who deliver the program) who are willing to initiate a program.	Qualitative Methods with Healthcare Professionals
Implementation	At the setting level, implementation refers to the intervention agents’ fidelity to the various elements of an intervention’s protocol, including consistency of delivery as intended and the time and cost of the intervention. At the individual level, implementation refers to clients’ use of the intervention strategies.	Compliance (attendance logs, SIRAS, exercise adherence questionnaire) Process evaluation through Qualitative methods
Maintenance	The extent to which a program or policy becomes institutionalized or part of the routine organizational practices and policies. Within the RE-AIM framework, maintenance also applies at the individual level. At the individual level, maintenance has been defined as the long-term effects of a program on outcomes after 6 or more months after the most recent intervention contact.	12-month outcome measures Process evaluation through Qualitative methods

A process evaluation will be embedded in the study. The process evaluation is key in understanding the why and the how of any intervention by examining its implementation, mechanisms of impact and contextual factors. The MRC has developed a set of guidelines for the conduct of process evaluations [74]. MRC recommends a basic framework for process evaluation with a different emphasis at each stage of the study. In the pilot phase, the key would be understanding the feasibility and intervention design optimization. In the main trial phase, the focus is on the fidelity of actual delivery, context and mechanism of impact. Context includes anything external to the intervention that may act as a barrier or facilitator to its implementation. The mechanism of impact seeks to identify the potential causal pathways that resulted in the changes seen.

In addition, the Global Alliance for Musculoskeletal Health (GMUSC) have proposed a framework to help individuals and organization with the planning, implementation and evaluation of models of care (MoC) in MSK health [75]. The implementation and evaluation framework in this study will utilize all 3 frameworks by using RE-AIM framework to guide the focus areas, the MRC process evaluation to understand the underlying mechanisms and the GMUSC framework to ensure system-level relevance for scalability. Results from the study will be reported according to the Standards for Reporting Implementation Studies (StaRI) [76].

### Qualitative study methodology

A combination of deductive and iterative approaches will be used. A literature review will be conducted to generate themes for the study topic guide. A combination of questionnaires and semi-structured interviews will be conducted based on the topic guide. Purposeful sampling with both healthcare professionals and patients involved in the study will be used to identify appropriate participants for interviews.

Interviews will be conducted by an independent assessor with previous experience in qualitative research not directly involved in the care of the patients. Any interviewer pre-existing bias will be identified and recorded. Transcripts and audio recordings will be stored digitally and analysed using a qualitative analysis program to code data, link concepts, examine similarities and differences and review patterns and themes. Coding will be done iteratively.

Themes emanating from transcripts will be identified through a framework method approach done by 2 independent researchers supervised by a senior researcher with significant experience in qualitative research to ensure inter-observer reliability. Using the framework method, the data is reduced through a matrix comparing categories of data [77]. The framework method has been shown to be an appropriate method for the evaluation of multidisciplinary complex intervention. Data will be sampled till saturation. Results will be reported according to the Consolidated criteria for reporting qualitative research (COREQ) guideline [78].

## Discussion and conclusion

A rapidly aging global population has resulted in an OA epidemic that is currently being poorly managed on a global scale. CONNACT is a community-based, multidisciplinary 12-week program that uniquely uses an individualized approach based on a triaging criterion to tailor the treatment to each patient coupled with a strong emphasis on patient activation and self-management. Traditional MoC for knee OA utilize a step-wise approach where all patients get baseline education, exercise and weight loss advice before gradually moving up the treatment ladder if treatment is unsuccessful [79]. In line with the “*right care*, delivered at the *right time*, by the *right team*, in the *right place*, with the *right resources*” philosophy, CONNACT proposes the use of an individualized approach through the use of a triaging criterion.

A complex intervention is defined by the MRC as an intervention that contains several interacting components [12]. There are several dimensions of complexity that can exist including the interaction between components of the control and intervention arms, difficulty of behaviours change required to deliver or receive the intervention, number of groups targeted, variability of outcomes to the degree of flexibility of intervention permitted. With rapidly evolving healthcare systems, complex interventions are being developed in the common drive to provide cost effective, sustainable care for patients. However due its inherent nature, there are issues in describing, developing, documenting and implementing complex intervention [80].

CONNACT MoC is a complex intervention that aims to promote long term sustainable behavioural change for patients with knee OA. In line with the MRC guidance for developing and evaluating complex interventions, building from a pilot feasibility study, this study protocol describes a comprehensive approach including an RCT, economic evaluation and process evaluation using a mixed method approach. The primary aim of this study is to determine the clinical effectiveness of the CONNACT MoC compared to usual care. The secondary aims are: a) To determine the cost-effectiveness and b) To develop an evaluation and implementation framework to inform large scale implementation for this MoC. The study will utilize an explanatory sequential mixed methods design where the qualitative data will be critical in providing context for the quantitative results allowing for a clearer interpretation.

Results from this study will help clinicians and healthcare administrators work side by side to avoid the “valley of death”, bridge the gap between research and clinical practice, guiding the sustainable and effective large-scale implementation of the CONNACT MoC for knee OA. In addition, CONNACT can serve as a basis for similar multidisciplinary complex MoC for chronic degenerative musculoskeletal conditions to be developed in line with the MRC guidelines.

## Data Availability

Not applicable.

## Abbreviations

CONNACT: Collaborative Model of Care between Orthopaedics and Allied Health Professionals Trial
MSK: Musculoskeletal
OA: Osteoarthritis
MoC: Model of Care
RCT: Randomized Controlled Trial
NICE: National Institute of Health and Care Excellence
ACSM: American College of Sports Medicine
NEMEX: Neuromuscular Exercise
OARSI: OA Research Society International
KOOS: Knee Injury and OA Outcome Score
EQ-5D-5L: EuroQol 5 dimensions 5 level
BMI: Body Mass Index
PHQ-4: Patient Health Questionnaire 4
PEG: Pain, Enjoyment, General Activity Scale
ACT: Acceptance and Commitment Therapy
FFQ: Food Frequency Questionnaire
ITT: Intention-to-treat
PAM: Patient Activation Measure
GPE: Global Perceived Effect
PASS: Patient Acceptable Symptom State
SIRAS: Sports Injury Rehabilitation Adherence Scale
PI: Principal Investigator
SD: Standard Deviation
GLMM: Generalized Linear Mixed Model
